#### Missing Data Handling

As the primary strategy to handle missing data, the longitudinal constrained analysis assumes that the probability of missing outcome data is not related to the missing data but to some of the observed measured data in the model (missing at random). Our models will use a restricted maximum likelihood estimator to handle missing data. The use of the restricted maximum likelihood estimator will enable us to effectively handle the potential bias introduced by differential attrition as it allows for the estimation of unbiased fixed-effects coefficients and appropriately accounts for the variability introduced by random effects.

#### Sensitivity Analysis

The frequency and percentage of participants with missing data at T0, T0.5, T1, and T2 will be summarized for the primary and secondary outcomes. In addition, baseline and demographic characteristics will be summarized for those with and without missing data for the primary outcome measure (at T0, T0.5, T1, and T2) to explore the missing data assumption and identify and include in the relevant models any variables not included in the target primary analysis that are potentially associated with missingness.

### Monitoring

#### Data Monitoring

In partnership with the trial sponsor, we have determined that the planned work is of low risk and, thus, a data monitoring committee is unneeded. Participant data will be monitored during the study for adverse events and managed by the responsible researcher. If adverse events are severe, an independent data monitoring committee will be formed in consultation with the trial sponsor to evaluate whether the trial needs to be discontinued.

#### Harms

To manage and minimize risks, potential participants will be informed (before consent) of the marginal risk of distress and emotional discomfort when responding to survey questions about symptoms of depression, anxiety, and suicidal ideation. Participants will be informed of their right to withdraw from the study at any point. To address potential distress, in the plain-language statement, we indicate that, should participants experience discomfort or distress because of their participation in the study, they can contact the study lead or one of the provided referral sources. In addition, we will provide details of a range of psychological service providers if they wish not to take up the aforementioned option, including one specifically related to meditation-related difficulties. In the prescreening questionnaire, for any participants who report experiencing mild to severe symptoms of depression or slight to severe symptoms of suicidal ideation, an automated message will appear at the end that refers the participant to psychological support services.

For meditation-related risks, participants will be asked each week whether they have experienced an adverse event during the previous week that they believe may have been caused by their meditation practice. If an adverse event is reported, further screening measures will be administered to assess the nature and severity of the event and whether more follow-up is needed. In such cases in which follow-up is needed, an automated email will be sent to the principal researcher ([name]), who is a registered psychologist and, therefore, can personally assess what action is required. Adverse event and effect rates will be reported along with the study findings.

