#### Weekly Measures

During the intervention period, additional measures will be obtained weekly (ie, 7, 14, 21, and 28 days after the baseline survey).

*Mindfulness* practice will be assessed using the following items: (1) “In the past week, how many daily sessions of this study’s meditation program did you complete?” (response options: 0-7); (2) “In the past week, on the days you meditated with the study program, approximately how many minutes (on average) was each meditation session?”; (3) “In the past week, how many additional days did you practice meditation?” (response options: 0-7) and “In the past week, on the days you meditated in addition to the study program, approximately how many minutes (on average) was each meditation session?”; (4) “On the days you practised meditation, how many minutes per session did you practice? (this includes the guided sessions in the meditation program)” (response options: 0 to ≥60 min); and (5) “In the past week, how often did you engage in informal mindfulness practice? i.e. mindfully washing dishes, showering, walking etc.” (response options: none of the time to all of the time).

*Adverse events* will be assessed using a modified short form of the Meditation-Related Adverse Effects Scale [50].

*Sleep* will be assessed using a single item from the Sleep Quality Scale [33]: “During the past week, how would you rate your sleep quality overall?” (response options: *terrible*=1, *poor*=2-4, *fair*=5-7, good=7-9, and *excellent*=10).

*Expectancy* will be assessed using the following item: “How effective do you think your training so far has been for your [goal or motivation free-text field from run-in survey]?” (response options: not at all effective to very effective).

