### Sample Size

A meta-analysis of meditation apps [1] indicates a standardized mean difference (SMD) effect size of 0.29 (95% CI 0.14-0.45) for psychological well-being when comparing apps to controls. A more recent study [6] randomized participants to approximately 10 or 30 minutes of sitting or movement practice for 2 weeks. They estimated a difference in the effects on the WEMWBS between the sitting groups of short and long duration of SMD=0.2 to 0.25. To be conservative, we determined a target sample size with an SMD of 0.2.

On the basis of an SD in WEMWBS scores of 9.84 [55] and a within-individual correlation of 0.83 in repeated assessments of the WEMWBS [34], we would need a final sample size of 688 participants to achieve 80% power (at the 2-sided *P*=.02 significance level to correct for multiple comparisons between conditions) to detect a difference of 1.97 points (SMD=0.2) for each active condition (10, 20, and 30 min) compared to one another and with the minimal-dose condition. This would translate to approximately 172 participants per arm. These calculations were conducted using the *sampsi* package in Stata (StataCorp).

Meditation app studies indicate overall retention rates of approximately 60% for active mindfulness meditation interventions [1]. Given our use of a run-in period, the aim of which is to allow participants who are most likely to disengage to do so before randomization, we anticipate postrandomization retention rates approximating 80%. In total, we will then recruit on a rolling basis until we achieve the required sample size at randomization of 860.

We will aim to recruit the full sample by March 31, 2025. We will conduct an interim analysis at this stage if the sample is at <90% of the target. If the sample is at ≥90% of the target by March 31, 2025, recruitment will be terminated. If continued recruitment is necessary (ie, we recruit <90% of the sample by March 31, 2025), recruitment will continue until the target sample is reached or 6 months (from March 31, 2025) have elapsed (whichever occurs first). If an interim analysis is required, the team member who undertakes this analysis will not implement the final analysis (as they will need to be unblinded). Other members of the team will undertake the final analysis and will alter the arm designation in the analytic code to further blind results relative to the interim analysis.

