This study is being conducted entirely online. This has the advantage of allowing participants to practice in their homes and other familiar ecologically valid settings, although it also has the limitation of researchers having little control over the research environment. However, a common problem with internet-based interventions is high dropout rates and low adherence. Our primary analysis is to test the effectiveness of different doses, and therefore, our data will be analyzed on an intention-to-treat basis. As such, we are most concerned with the problem of high dropout rates. To minimize dropouts, we are offering financial inducements for participants to continue honestly reporting their practice amount and responding to questionnaires regardless of whether they are still completing the intervention. However, it is still in our interest to have high rates of adherence given that we will also analyze data on a per-protocol basis (ie, as secondary analyses only). To this end, we are using a run-in period to identify and exclude participants who are most likely to drop out and not complete the intervention before randomization. Given this use of the run-in period, we cannot make inferences about the likely adherence to similar mindfulness interventions in real-world settings. Therefore, while the use of a run-in period strengthens internal consistency, it introduces a selection bias. We will attempt to quantify this by reporting sociodemographic data and measures of mental health and well-being for people that complete the run-in period and compare them against those of people who do not. Despite the use of a run-in period, we still anticipate that adherence rates are likely to vary across dosage groups, with lower adherence at higher doses. This may limit our capacity to make inferences about the efficacy of different doses for the per-protocol analyses.

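### The weekly harm question looks back one week with no catch-up described, so a short-lived event in a week whose survey is missed is not captured by the scheduled question

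*Protocol article*

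**What the plan says.** All references are to the protocol article.

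- **Recall window (Monitoring, Harms).** "participants will be asked each week whether they have experienced an adverse event during the previous week", limited to events the participant attributes to meditation.
- **Trigger for further assessment (same section).** "If an adverse event is reported, further screening measures will be administered to assess the nature and severity of the event". Where follow-up is needed, an automated email goes to the principal researcher.
- **Timing (Outcomes, Weekly Measures).** During the intervention, "additional measures will be obtained weekly (ie, 7, 14, 21, and 28 days after the baseline survey".
- **Instrument (same section).** Adverse events "will be assessed using a modified short form of the Meditation-Related Adverse Effects Scale". The recall period of that form is not given.
- **Reporting (Harms).** "Adverse event and effect rates will be reported along with the study findings".
- **Use of the data (Strengths and Limitations).** The article cites a hypothesis that adverse experiences become more likely at higher doses. It says the design will let the team explore whether higher doses carry more risk, and that adverse experiences are tracked in both the intervention and the follow-up period.
- **Expected loss (Sample Size).** "we anticipate postrandomization retention rates approximating 80" percent, as one overall figure.

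**The concern.** The recall window and the survey interval are both one week, so the question covers the whole course only if every weekly survey is completed. Suppose a participant has a distressing but short experience in week 2, skips the day 14 survey and returns on day 21. They are then asked about week 3 only. The article describes no question that reaches back over the gap and no contact with people who miss a survey. This needs no dropout; one missed survey is enough.

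Two things are at stake. The harm rates are to be published, and events in missed weeks would be absent from them. The article also wants to compare harm across doses, where both the number of events seen and their balance between arms matter. An event that was never asked about cannot be recovered in the analysis, so this has to be settled in the questionnaire and cannot be left to an analysis plan.

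**Working it through.** **The plan's own loss figure.** 688 / 0.80 = 860, which matches the "required sample size at randomization of 860". With equal allocation to four arms, 860 / 4 = 215 per arm. The article gives no figure for harm.

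**Coverage of the schedule.**

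| Survey | Period asked about | If missed, next scheduled question covers |
|---|---|---|
| Day 7 | days 1–7 | days 8–14 |
| Day 14 | days 8–14 | days 15–21 |
| Day 21 | days 15–21 | days 22–28 |
| Day 28 | days 22–28 | none described |

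In no row does the next question reach back. A lasting or repeated effect could still be reported at the next survey, so the gap concerns transient events. Under Participant Compensation the week 1 and week 3 surveys pay Aus $5, against Aus $15 at midintervention and Aus $25 at postintervention. Day 7 and day 21 are therefore the harm time points with the smallest incentive.

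**Illustration of size.** The article gives neither harm risks nor response by arm, so every input below except 215 per arm is an assumption. Let *p* be the true risk, *m* the share of events falling in a missed week and not captured later, and *e* a further share lost because the event itself stopped the person responding. With all randomised participants as denominator:

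observed risk = *p* × (1 − *m*) × (1 − *e*); events lost per arm = 215 × (*p* − observed risk).

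For 4 min against 30 min with *e* = 0:

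| True risk | Loss *m* | Observed risk | Risk ratio | Events lost |
|---|---|---|---|---|
| 10% v 20% | 20% v 20% | 8.0% v 16.0% | 2.00 | 4.3 v 8.6 |
| 10% v 20% | 15% v 25% | 8.5% v 15.0% | 1.76 | 3.2 v 10.75 |
| 10% v 20% | 10% v 30% | 9.0% v 14.0% | 1.56 | 2.15 v 12.9 |
| 10% v 10% | 20% v 20% | 8.0% v 8.0% | 1.00 | 4.3 v 4.3 |
| 10% v 10% | 10% v 30% | 9.0% v 7.0% | 0.78 | 2.15 v 6.45 |

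Example, second row: 0.10 × 0.85 = 0.085; 0.20 × 0.75 = 0.150; 0.150 / 0.085 = 1.76; 215 × 0.015 = 3.2; 215 × 0.050 = 10.75.

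Power for the first row (two-sided 0.05, 215 per arm) falls from 0.83 with complete capture to 0.72. With true risks of 5% and 10% and the same equal loss it falls from 0.50 to 0.42.

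Adding *e* = 0.25 in both arms of the first row gives 6.0% v 12.0%; *e* = 0.50 gives 4.0% v 8.0%. The ratio stays at 2.00 and power drops to 0.59 and 0.42.

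**What this shows.** Equal loss leaves the ratio alone and costs events and power. The ratio moves only when the lost share differs by arm. With equal loss the 30-minute arm loses more events only if its true risk is higher.

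**The case against.** The strongest reply is that surveys are deliberately separated from practice. Under Participant Compensation, people are still invited to answer after they stop meditating, and they are paid for surveys and not for practice. Someone who stops the course because of a bad experience therefore still has a reason to report it. This stands, and it limits the point.

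A reader might infer that harm-related loss falls mostly on the high-dose arms, because "we still anticipate that adherence rates are likely to vary across dosage groups, with lower adherence at higher doses". The documents do not support that. The sentence is about adherence, which the article treats separately from survey response; the Objectives leave retention by arm as a question to explore; and the 80% is an overall retention figure, not a weekly response rate by arm. Unequal loss is a possibility only.

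Two other strong readings also fail. Nothing says a missed survey will be counted as no event: the denominator is not stated, and an article may leave it to the analysis plan. If assessed weeks were the denominator, non-response unrelated to harm would not bias the rate, though it would still cost events. Nor are affected participants left without help. The Harms section gives them the study lead, referral sources and a provider for meditation-related difficulties. What a silent non-responder lacks is contact started by the protocol.

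Finally, the Figure 2 legend lists the adverse effects scale and the figure is not shown. An assessment at T1 or T2, possibly with longer recall, cannot be ruled out. That could narrow the gap. It does not alter the one-week window stated in the Harms text.

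**Conclusion.** The point holds in a limited form. The text fixes a one-week recall at four weekly times, makes further assessment depend on a reported event, and describes no catch-up. A transient event in a week whose survey is missed is therefore not captured by the scheduled question. Harm rates may be understated. The comparison of harm by dose loses power, and is biased only if the lost share differs by arm.

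The true size cannot be derived from the article. Under the assumed risks of 10% and 20%, the observed ratio runs from 2.00 (equal loss) to 1.56 (10% v 30% loss). If the true risks were equal, the latter loss would give 0.78, making the higher dose look safer. These figures assume each event is confined to one missed week and that all randomised participants are the denominator.

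There is a related mismatch to reconcile. Strengths and Limitations says adverse experiences are tracked through follow-up, while Weekly Measures schedules the harm measure only up to day 28, unless Figure 2 places it later. This is a modest weakness in harm capture, worth correcting because correction is cheap. It does not touch the primary analysis.

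**What to change.** 1. Reword the weekly item to ask about the time *since your last completed survey (or since the course began)*.
2. At T1 and T2, ask anyone with a missed week about the period still uncovered. Someone who misses day 28 can then be reached only at T2.
3. State in the text whether harm is assessed at T2, so that Weekly Measures, Figure 2 and Strengths and Limitations agree.

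The cost is one reworded phrase and one conditional question, with an amendment through the route in Protocol Amendments. Randomisation, the primary outcome and the sample size are unaffected. The downside is somewhat longer recall for those who missed a week, in a trial that already lists recall bias as a limitation; those who answer every week see the same window as now. If the wording changes while participants are in the course, record the date. Because allocation is in balanced blocks of 24, the change should reach all arms about equally.

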#### Auditing

Throughout the data collection phase, the research team will hold regular meetings to manage the project day to day and ensure that all procedures are being followed. The meetings will review recruitment progress, discuss any reported issues by participants, and anticipate and resolve any problems.

### Ethical Considerations

#### Research Ethics Approval

Approval has been obtained from the Human Ethics Team at the University of Melbourne’s Office of Research Ethics and Integrity (23299). The trial protocol has been developed consistent with the SPIRIT (Standard Protocol Items: Recommendations for Interventional Trials) 2013 statement [65]. Results will be reported using the CONSORT-EHEALTH (Consolidated Standards of Reporting Trials of Electronic and Mobile Health Applications and Online Telehealth) clinical trial reporting tool [66].

#### Protocol Amendments

If needed, the study researchers will prepare protocol amendments and will seek approval from the Human Ethics Team at the University of Melbourne. Any updates to the protocol will be reflected in the trial registration on ClinicalTrials.gov, and an updated version will be posted on the Open Science Framework website [22].

#### Consent

The consent form will be embedded within the study landing page in Qualtrics. Participants can provide informed consent to participate in the trial by checking the box at the bottom of the form. Only once informed consent is provided will the participant be able to advance to the prescreening measures.

#### Confidentiality

Data that identify participants will be retained in a separate, password-protected database on an encrypted University of Melbourne computer to which only the responsible researcher will have access. All participants’ data will be stored on a secure server by Unforgettable Research Services Pty Ltd (via Amazon Web Services). Amazon Web Services has extensive security measures, including rotating keys and a comprehensive identity management and permission system. All transmission of information across networks will occur in encrypted form. Only deidentifiable data will be stored online in perpetuity in line with open science best practices. All analyses will be conducted on deidentifiable data.

#### Participant Compensation

To promote study retention, participants will be reimbursed for the completion of surveys at each successive stage of the intervention: Aus $15 (US $9.75) for baseline measures (approximate completion time: 20 min), Aus $5 (US $3.25) for the surveys at the end of week 1 and week 3 (completion time: approximately 3 min each), Aus $15 (US $9.75) for the midintervention survey at the end of week 2 (completion time: approximately 15 min), Aus $1 (US $0.65) for each of the 24 daily surveys (completion time: approximately 24 min), Aus $25 (US $16.24) for postintervention measures (completion time: approximately 20 min), and Aus $20 (US $12.99) for follow-up measures (completion time: approximately 20 min). Total remuneration for participants who complete all surveys is Aus $109 (US $70.82), and they should take approximately 90 minutes to complete over the course of the study. In addition, participants who complete the prescreener will be entered into a draw for 1 of 10 Aus $100 (US $64.97) gift cards via GiftPay. Once eligible and enrolled, participants who successfully complete the run-in period will be entered into a further draw for 1 of 10 Aus $100 (US $64.97) gift cards via GiftPay. Participants will be invited to complete surveys regardless of whether they practice meditation or continue with the course, and no financial reward will be offered for completing meditation practice or listening to the guided practice audio instructions.

### Access to Data

Only researchers listed as authors of this manuscript will have access to the final trial dataset.

### Ancillary and Posttrial Care

The responsible researcher is a registered psychologist who will follow best clinical practices for follow-up and risk management. Given the low-risk nature of the intervention and the prescreening measures, it is not anticipated that additional posttrial care will be required.

### Dissemination Policy

Results will be published in peer-reviewed journals and presented at conferences. A lay summary will be disseminated to a wider audience via the University of Melbourne’s website and promoted via social media.

## Results

This is protocol version 1.1. Version 1.0 was uploaded to the Open Science Framework website in early May 2024 to coincide with the start of recruitment. This study has been prospectively registered at ClinicalTrials.gov with the identifier NCT06378450. Recruitment was paused approximately 6 weeks later after a significant number of participants were identified as being fraudulent and not meeting the eligibility criteria. At this time, <5% of the sample had been recruited. Additional screening procedures have been introduced, and recruitment reopened in October 2024. Version 1.1 of the protocol incorporates these minor changes. We estimate that the results will be published by March 2026.

## Discussion

### Overview

This pragmatic randomized controlled trial aims to conduct a thorough evaluation of the dose-response effects of mindfulness meditation. This will contribute to understanding how much mindfulness practice people need to engage in to promote improved well-being and other psychological outcomes.

The evidence base for dose-response effects in mindfulness meditation practices remains inconclusive. Empirical studies exploring variations in session lengths and frequencies have not consistently demonstrated significant differences in outcomes across different doses [5,7,8]. These studies have had limitations such as small sample sizes and brief overall program durations. Meta-analyses and meta-regression models have also produced mixed findings, with some indicating minor benefits from larger doses over smaller doses and others showing no significant effects [10]. However, these studies lack random allocation of participants to different doses, and therefore, the results may be subject to bias. Overall, current industry practice (advocating for doses as low as 5 min/d) and current research underscore a need for more rigorous studies to establish clearer guidelines on effective mindfulness practice dosages.

